## Participant Discontinuation/Withdrawal from the Study

Participants are free to withdraw from the study at any time. QI may discontinue or withdraw a participant from the study for the following reasons:

- The study participants suffer treatment-related intolerable adverse effects
- If the participant's headache gets worse
- The participant becomes pregnant
- The participant is unable to attend the study site for the follow-up visits
- The study participant does not comply with the prescribed regimen of the investigational drug
- The study terminated at a particular site either by site qualified investigator, principal investigator or due to any other reasons such as administrative
- If the participant meets an exclusion criterion (either newly developed or not previously recognized) that precludes further study participation

The reason for participant discontinuation or withdrawal from the study will be recorded on the CRF. Participants will be given the option to only withdraw from the study intervention, these participants will continue to be followed up till the end of study (visit 7) with the other assessments listed in SOA.

Participants who sign the informed consent form and are enrolled but do not receive the study intervention may be replaced. Study participants who sign the informed consent form and are enrolled receiving the study intervention and subsequently withdraw/discontinue will not be replaced.

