*a. If participant withdraw from the study intervention prior to visit 7 but consents to stay in the study, they will be followed up till visit 7 for all the other assessments, including bloodwork, eDiary and questionnaires. Site study team will provide guidance on IP administration and follow up with participant regarding their experience of IP administration at home. IP administration will not be completed at study site during the scheduled study visit.*

*b. Document titled “C4T Baseline Safety Screening Tool for Cannabis-related interventional trials”, also called “SCR Checklist” will be used by study team to document thorough medical history at visit 1, with Common Terminology Criteria for Adverse Events (CTCAE) grade level to be applied with each reported medical history condition.*

*c. Participants will self-administer the investigational product orally following a dosing calendar and all dosing calculations will be based on weight at baseline (visit 1), unless there is a significant body weight change that would affect dosing. If participant’s body weight increases or decreases for 10% or above comparing with baseline data, site investigator will contact study PI [name] for further instructions regarding dose change or participant withdrawing. The decision will be made on a case-by-case basis to protect participant’s safety, and in the meanwhile minimize negative impact on data integrity.*

*d. Any ongoing co-existing medical condition at visit 1 will be followed up by site study team at follow-up visits to document changes.*

*e. Both urine and blood pregnancy tests will be completed at visit 1. Blood pregnancy test will be completed from visit 2- visit 7.*

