# STUDY INTERVENTION DISCONTINUATION AND PARTICIPANT DISCONTINUATION/WITHDRAWAL

## Dose limiting toxicity and Discontinuation of Study Intervention

Adverse events are categorized using the Common Terminology Criteria for Adverse Events (CTCAE version 5.0 dated 27 Nov 2017). If any of the following occur the participant will not move up to the next dose level (dose limiting toxicities):

1. Parental/youth report complaints of moderate mood elevation defined as exaggerated feelings of well-being which is disproportionate to the events and stimuli (Euphoria Grade 2)
2. Somnolence Grade 2 which includes moderate sedation (sleepiness and drowsiness) that limits instrumental activities of daily living
3. Cannabis-attributed diarrhea, Grade 2 or more defined as an increase of 4 - 6 stools per day over baseline; moderate increase in ostomy output compared to baseline; limiting instrumental activities of daily living
4. Unexplained tachycardia (w/out pain, fever, anemia etc.) requiring medical intervention
5. Unexplained hypotension requiring medical intervention
6. Non-infectious conjunctivitis Grade 2 defined as moderate decrease in visual acuity (best corrected visual acuity 20/40 and better or 3 lines or less decreased vision from known baseline) characterized by inflammation, swelling and redness to the conjunctiva of the eye.
7. Serious adverse events requiring hospitalization
8. Discretion of the participant, physician, or parents

Discontinuation from the study intervention does not mean interruption from the study, and remaining study procedures should be completed as indicated by the study protocol.

There will be no replacement of the study participants who were administered the investigational product, withdraw from the study, and lose follow-up (after signing an informed consent form). The main reason for the withdrawal of participants from the study will be noted in the participant's Case Record Form (CRF). The site investigator should contact the participants who fail to report during the follow-up visits which will be documented in the CRF.

Adverse events (AEs) and SAEs (Serious Adverse Events) will be reported according to Health Canada and Institutional regulations and reviewed by the data safety monitoring board (DSMB). The DSMB will hasten safety review if death is deemed related or potentially relevant to CBD-enriched CHE used in the study as the investigational product.

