### Time Period and Frequency for Event Assessment and Follow-Up

The occurrence of an adverse event AE or SAE may come to the attention of study personnel during study visits and interviews of a study participant presenting for medical care or upon review by a study monitor.

All AEs, including local and systemic reactions not meeting SAEs' criteria, will be captured on the appropriate case report form (CRF) of REDCap. Information to be collected includes event description, time of onset, clinician's assessment of severity, relationship to study product (assessed only by those with the training and authority to make a diagnosis), and time of resolution/stabilization of the event. All AEs occurring while on the study must be documented appropriately regardless of relationship. All AEs will be followed to an adequate resolution.

Any medical condition present at the time that the participant is screened will be considered a baseline and not reported as an AE. However, if the study participant's condition deteriorates during the study, it will be recorded as an AE. Changes in the severity of an AE will be documented to allow an assessment of the duration of event at each level of severity to be performed. AEs characterized as intermittent require documentation of onset and duration of each episode.

The study team will record all reportable events with start dates occurring any time after informed consent is obtained and for the duration of study participation. At each study visit, the investigator will inquire about the occurrence of AE/SAEs since the last visit. Events will be followed for outcome information until resolution or stabilization.

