### Reporting of Pregnancy

Pregnancy tests (detection of human chorionic gonadotropin) will be completed using blood samples collected to investigate cannabinoid blood levels. At visit 1, a urine pregnancy test will be added on top of the blood pregnancy test to exclude patients with positive result from enrollment. Eligibility confirmation will still depend on the visit 1 blood pregnancy test result. Any participant who becomes pregnant will be offered to counsel and will be withdrawn from the study (investigational product use terminated).

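### Section 8.2 lets the QI withdraw a participant from the study, not only from the product, for a poor trial outcome; it should say that follow-up to visit 7 is the default (minor wording fix)

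*Protocol*

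**What the plan says.** Section 8.2 (Participant Discontinuation/Withdrawal from the Study) states: "QI may discontinue or withdraw a participant from the study for the following reasons". Seven reasons follow: intolerable treatment-related adverse effects, worse headache, pregnancy, inability to attend, non-compliance with the product, termination of the site or study, and an exclusion criterion that precludes further participation. The reason is to be recorded on the CRF.

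Three places describe stopping the product while staying in the study:

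- Section 8.1: "Discontinuation from the study intervention does not mean interruption from the study, and remaining study procedures should be completed as indicated by the study protocol".
- Section 8.2, shortly after the QI's list: "Participants will be given the option to only withdraw from the study intervention", with follow-up to visit 7.
- Table 1, footnote a, for participants who withdraw from the product and consent to stay: "they will be followed up till visit 7 for all the other assessments, including bloodwork, eDiary and questionnaires".

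Section 9.3.8 on pregnancy says: "Any participant who becomes pregnant will be offered to counsel and will be withdrawn from the study (investigational product use terminated".

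On replacement, 8.2 says that treated participants who "subsequently withdraw/discontinue will not be replaced". On events, 9.3.4 says: "Events will be followed for outcome information until resolution or stabilization".

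**The concern.** In the Synopsis the primary endpoint is treatment-emergent adverse events, and the secondary endpoints include headache-free days and headache pain intensity. Two of the QI's reasons for ending study participation are therefore bad results on the trial's own endpoints. A rule that lets observation stop because the outcome was poor permits data to go missing in exactly the participants who did worst. No analysis can restore data that were never collected, so this belongs in the protocol's conduct rules.

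The product-only path would prevent this, but in 8.2 and footnote a it is worded as something the participant chooses. Nothing says what happens when the QI initiates the stop, and three sites could apply the same text differently. At stake are off-product safety follow-up and later headache and questionnaire data, in a 20-person trial that does not replace treated participants.

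**Working it through.** The protocol gives no figure for this point (no dropout rate, no assumption about withdrawals). The check sets the texts side by side and counts what full withdrawal would remove.

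**1. Who initiates the stop, and from what?**

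| Text | Initiator | Stop applies to | Follow-up |
|---|---|---|---|
| 8.2, list of reasons | QI (discretionary) | Study | Not stated |
| 8.1, closing statement on discontinuation | Not limited | Product | Remaining procedures completed |
| 8.2, option sentence | Participant is offered it | Product | To visit 7 |
| Table 1, footnote a | Participant, who consents to stay | Product | To visit 7 |
| 9.3.8, pregnancy | Protocol rule | Study, with product use ended in parentheses | Not stated |

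No row says that the product-only path governs, or must be offered first, when the QI acts under the 8.2 list. The 9.3.8 wording can be read either way.

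**2. How many reasons are outcomes?** Adverse effects and headache: 2 of 7. Pregnancy and non-compliance are not endpoints, but they too are reasons to stop the product rather than to stop observing. That makes 4 of 7 that fit product discontinuation and 7 − 4 = 3 that fit study withdrawal.

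**3. What would be lost?** Inputs: visits 3 to 7 fall on days 60, 90, 120, 150 and 180 (Table 1). Dosing starts the day after visit 2 (Dosing and Administration), so five scheduled visits follow it. Assume that the visit at which withdrawal occurs is completed. Days lost = 180 − visit day; visits lost = 7 − visit number.

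| Withdrawn at | Visits lost (of 5) | Scheduled days lost | Post-baseline physical exams left (of 1) |
|---|---|---|---|
| Visit 3 | 7 − 3 = 4 | 180 − 60 = 120 | 0 |
| Visit 4 | 7 − 4 = 3 | 180 − 90 = 90 | 0 |
| Visit 5 | 7 − 5 = 2 | 180 − 120 = 60 | 0 |
| Visit 6 | 7 − 6 = 1 | 180 − 150 = 30 | 0 |

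Table 1 schedules the physical exam and the CUDIT-SF only at visits 1 and 7, so the single post-baseline value of each goes with visit 7. The liver and renal tests, diary and questionnaires go with the missed visits and days. Each such participant is 1/20 = 5% of the planned sample.

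**4. What stays?** The triggering event is recorded and followed to resolution or stabilization (9.3.4), and the reason for withdrawal is on the CRF (8.2). Section 10.3 names withdrawal among the circumstances covered by the analysis population. The planned primary summary is descriptive, by dose level (10.3.2), and time after the product is stopped adds no exposure at any higher dose level.

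**5. New events after a full withdrawal.** Section 9.3.4 covers events "with start dates occurring any time after informed consent is obtained and for the duration of study participation", while 9.3.5 runs to the end of visit 7. The two agree as long as the participant stays in the study. They part only if full withdrawal is used, so the fix to 8.2 removes the question.

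**The case against.** The strongest reply is that the protocol already settles this. The QI's power is permissive, whereas the option sentence in the same section is mandatory and makes no exception for stops initiated by the QI. A permissive power and a mandatory offer do not conflict, so the natural reading is that anyone stopped for a listed reason is offered continued follow-up. Section 8.1 is also not limited to the participant's choice: its list of dose-limiting events includes physician discretion, and its statement on discontinuation is general. The parenthesis in 9.3.8 can be taken to explain withdrawal as ending product use. And discretion to spare a minor with intolerable effects monthly venipuncture and a daily diary is a defensible safety provision.

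Most of this stands. It makes the product-only reading the probable intent and keeps the point small. It does not close the gap: the option sentence and footnote a describe a choice by the participant, the list in 8.1 literally governs whether to escalate the dose, and none of them says that it limits the separate power to withdraw from the study.

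Two stronger readings should be set aside. A reader might infer that 8.2 requires removal of participants who do badly; it does not, since the power is discretionary and the alternative stands in the same section. A reader might also infer that the primary endpoint is biased. The text does not support that either: the triggering event is counted and followed, withdrawn participants stay in the population, and the lost time is mostly off product. The missing CUDIT-SF matters little, because it asks about cannabis other than the study oil.

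**Conclusion.** The point holds as a minor, inexpensive improvement. Section 8.2 permits, without requiring, full study withdrawal for two trial outcomes, and 9.3.8 words pregnancy in the same way. The existing product-only path is probably meant to apply but is not stated to cover stops by the QI.

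For each participant fully withdrawn at visits 3 to 6, the loss is 4 to 1 of five visits and 120 to 30 scheduled days, plus the only post-baseline physical exam. These counts describe lost follow-up and do not measure bias. The number of participants affected is unknown, since the protocol gives no withdrawal rate. The practical loss is off-product safety tests and later headache and questionnaire data, concentrated in those who did worst.

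The conclusion that the primary summary is little affected assumes the population in section 10.3 (at least one dose). The Synopsis asks for at least one month on product, under which a withdrawal in the first month of dosing would drop out of the analysis.

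**What to change.** In 8.2, list intolerable adverse effects, worse headache, pregnancy and non-compliance as reasons for which the QI may discontinue the intervention. State that the existing follow-up to visit 7 (footnote a) is the default if the participant agrees, whoever initiates the stop. Keep study withdrawal for withdrawn consent or assent, loss to follow-up or inability to attend, site or study termination, and an exclusion criterion that truly precludes participation. In 9.3.8, say that a pregnant participant is withdrawn from the study intervention, with safety follow-up to visit 7.

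The cost is new wording in two sections and a few off-product visits for those who agree to them. The QI's authority to stop the product and the participant's right to leave are unchanged.

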## Lost to Follow-Up

Participants will be considered lost to follow-up if they fail to return for all the follow-up visits and cannot be contacted by the study staff.

The following actions must be taken if a participant fails to return to the clinic for a required study visit:

- The site will attempt to contact the participant and reschedule the missed visit and counsel the participant on the importance of maintaining the assigned visit schedule and ascertain if the participant wishes to and/or should continue in the study
- Before a participant is deemed lost to follow-up, the investigator, research coordinator or designee will make every effort to regain contact with the participant (where possible, three telephone calls, and, if necessary, a certified letter to the participant's last known mailing address or local equivalent methods). These contact attempts should be documented in the participant's medical record or study file
- Should the participant continue to be unreachable, they will be considered withdrawn from the study with a primary reason for loss to follow-up

# STUDY ASSESSMENTS AND PROCEDURES

## Measures of Effectiveness

Participants will participate in the study for 6 months, including the follow-up visits. Participant data will be collected and entered into electronic CRF in a Research Electronic Data Capture (REDCap) database. The following assessment will take place for the study participants:

**Physical examination**

During the baseline visit, the eligible study participants will undergo physical assessments, including height, weight, and calculation of Body Mass Index (BMI), evaluation of organ system, motor, and vision. Blood work will assess liver and renal safety lab tests, plasma concentration of cannabinoids and saliva samples for pharmacogenomic analyses. All the female participants who have experienced menarche will have pregnancy test at baseline and at all follow-up visits. At the time of screening, participants will receive an electrocardiogram should they not have had one in the previous 3 months. Vital signs and weight will be collected at every visit. The weight obtained at the baseline visit will be the weight used to determine the dose of investigational product throughout the study.

**Electronic headache diary**

The study participant will be instructed to maintain the electronic headache diary, monitor and report the information related to the intensity of headache on the NRS, and use of the rescue medication. Information about headache triggers will also be collected. The daily diary was developed in collaboration with the youth advisors. The administration will incorporate best practices in daily diaries in adolescents and feedback from patients with chronic pain and families interviewed about the use of in-home longitudinal ecological momentary assessment tools. [[122](#_heading=h.4gjguf0)] The NRS is a validated tool used to record daily self-reports of headache intensity from visit 1 until the end of the study.[[123](#_heading=h.2vor4mt)] Participants will rate the intensity of pain from 0 to 10, 0 means no hurt, 10 represents the worst hurt you could ever imagine. The efficacy of the investigational product in treating the chronic headache will be assessed in reducing the intensity of headache from baseline to each follow-up visit. REDCap will be used to complete electronic diaries. Daily data from the electronic headache diaries will be transferred to the server. Based on the intensity of the NRS, the study participant will be categorized into the severity of the headaches. The mild headache will vary in intensity between 1-5, moderate between 6-8, and severe between 9-10.[[124](#_heading=h.1au1eum)]

**Actigraphy**

All the study participants will be given an option of using a wrist worn device to help them keep track of their sleep parameters. Participants will be notified that data collected on the device won’t be used in this study.

**PROMIS measures**

Patient-Reported Outcomes Measurement Information System (PROMIS) is the patient-centric measure that evaluates adults and children's social, mental, and physical health. [[125](#_heading=h.3utoxif)] We will be using the PROMIS tools to measure the outcomes in the patients, pain, sleep, depressive symptoms, feelings, and quality of life. The study participants will administer the following PROMIS measure.

**Pediatric Sleep-Related Impairment- Short Form 8a scale**

The pediatric sleep-related impairment- short form 8a scale is the PROMIS tool used to assess perceptions of sleepiness during usual awake hours and reported impairments during the day associated with sleep problems or daytime sleepiness. Mainly this tool estimates the sleepiness during the daytime, sleep offset, and its impact on cognitive, other activities, as well as emotional impact. The Pediatric Sleep-Related Impairment- Short Form 8a scale is a reliable generic scale with good validity and internal consistency.[[126](#_heading=h.29yz7q8)]

**Pediatric Anxiety Symptoms- Short Form 8a scale v2.0**

The pediatric short form v2.0 Anxiety scale is a (PROMIS) tool that assesses the self-reported fear (fearfulness, panic), anxious misery (worry, dread), hyperarousal (tension, nervousness, restlessness), and somatic symptoms related to arousal (racing heart, dizziness). The symptoms of autonomic arousal and experience of threat reflect the anxiety. The pediatric short form v2.0 Anxiety scale is non-disease specific, and it can assess the anxiety in the children over the past seven days. The literature reports the excellent reliability and validity of the Pediatric Short Form v2.0 - Anxiety - 8a scale. [[127](#_heading=h.p49hy1)]

**Pediatric Depressive Symptoms Short Form 8a scale v2.0**

Pediatric Short Form v2.0 - Depressive Symptoms 8a is a PROMIS tool that is used for assessment of negative mood like sadness or guilt, self-criticism, worthlessness (self-views), loneliness, interpersonal alienation (social cognition) and decreased positive affect and engagement, which includes loss of meaning, interest and purpose. However, this scale does not assess somatic symptoms such as changes in appetite and sleeping patterns. This scale is again generic rather than disease-specific. Pediatric Short Form v2.0 - Depressive Symptoms 8a scale possesses good test-retest reliability and validity of administration across groups.[[128](#_heading=h.393x0lu)]

**Pediatric Pain Interference**

The Pediatric Pain Interference, PROMIS tool assesses the self-reported consequences of pain on the essential aspects of a patient’s life, which comprises the extent by which pain interferes with activities of a person such as cognitive, emotional, social, physical, and recreational activities. The pediatric pain interference scale is generic, not focusing on any of the disease-specific conditions. The Pain Interference items utilize a 7–day recall period (items include the phrase "the past 7 days"). Varni JW et al. reported that PROMIS Pediatric Pain Interference Scale contains the item set that provides maximal test information at the mean of 50 on the T-score metric. [[129](#_heading=h.1o97atn)]

